### Intervention

The intervention is a digital emergency referral platform, which encompasses a mobile app and web-based application—the KP MTI Referral Application. The platform offers a standardized electronic referral form, bed availability in real time, unique referral identifiers, and triage by urgency (emergency, urgent, and routine; Table 1). The platform has a 2-way communication feature that enables receiving specialists to give clinical management advice to referring health care professionals without the latter necessarily transferring the patient. Automated notifications are set based on the urgency category, with time-sensitive alerts on emergency and urgent referrals and regular alerts on routine referrals. This urgency-stratified method does not cause alarm fatigue linked to universal reminders. Figure 1 illustrates the referral process workflow. Figures 2 and 3 show mobile app interfaces.

**Table 1 table1:** Platform components and their purpose.

Platform component	Function	User group
Standardized electronic referral form	Captures demographics, clinical summary, diagnosis, and urgency category	Referring physicians, nurses, and medical officers
Image and document upload	Transmits clinical photos and imaging for remote specialist review	Referring health care professionals
Real-time bed availability display	Enables informed referral destination selection	All referring health care professionals
Urgency triage classification	Stratifies referrals as emergency, urgent, or routine to prioritize responses	Referring health care professionals and triage nurses
Unique referral identifier	Enables end-to-end tracking of each referral from initiation to outcome	All users and administrators
Bidirectional communication function	Allows specialists to provide management advice without requiring transfer	Receiving specialists and referring health care professionals
Urgency-based automated notifications	Alerts for emergency and urgent referrals and standard notifications for routine referrals	Receiving specialists and bed managers

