### Participants and Recruitment

The research will engage health care professionals such as emergency physicians, consultants, medical officers, nurses, bed managers, and administrative personnel who have access to referral dashboards to monitor and coordinate. The patients or their legal attendants who undergo the referral process within the study period will also be invited to participate.

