### Eligibility Criteria

In the quantitative component, all the emergency referral records created via the digital platform within the 6-month study period will be considered. Records will be omitted when they are not complete, marked as duplicates, or created in the process of system testing. In the qualitative component, health care providers will be eligible if they have made at least one referral through the digital platform. Patients or attendants will be included if they have been referred to a hospital via the platform. Those who do not give consent will be excluded.

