### Sample Size and Sampling

The quantitative part will use a census-based cohort design: all the referral records created via the platform over the 6-month pilot will be considered. According to the administrative referral logs of LRH, KTH, and HMC, it is estimated that 5000 to 7000 emergency referrals will be made. As the sample size of a census-based implementation study cannot be calculated using formal power, the rationale behind the sample size is the expected volumes of institutional referrals. For the qualitative component, health care providers will be selected using stratified purposive sampling to ensure representation across facility levels (primary, secondary, and tertiary), clinical roles (physicians, nurses, and administrators), and geographic locations (urban and rural). Recruitment will continue until thematic saturation is reached, with an anticipated sample of 20 to 30 individual interviews and 4 to 6 focus group discussions involving 6 to 8 participants each. Patients and attendants will be recruited using convenience sampling at the time of referral completion.

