### Interview and Focus Group Topic Guide

The semistructured interview and focus group discussion topic guide (Multimedia Appendix 2) covers 7 domains: platform usability, fit with clinical workflow, barriers to adoption, facilitators, perceived impact on referral decisions, bidirectional communication, and recommendations for scale-up.

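### The only provider eligibility rule for the qualitative component, having made a referral on the platform, cannot deliver the sample the protocol asks for: administrators and bed managers are shut out, and receiving specialists largely so

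*Protocol article*

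**What the plan says.** Under Eligibility Criteria, the protocol article gives one condition for providers in the qualitative component: "health care providers will be eligible if they have made at least one referral through the digital platform". Apart from the need to consent, no other condition and no alternative route is given.

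Three other sections describe who is wanted:

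- Participants and Recruitment lists "emergency physicians, consultants, medical officers, nurses, bed managers, and administrative personnel who have access to referral dashboards", the last group for monitoring and coordination.
- Sample Size and Sampling calls for stratified purposive sampling of providers with "representation across facility levels (primary, secondary, and tertiary), clinical roles (physicians, nurses, and administrators" as strata, plus urban and rural location. It anticipates 20 to 30 interviews and 4 to 6 focus groups of 6 to 8 people.
- Interview and Focus Group Topic Guide names seven domains, among them "barriers to adoption, facilitators, perceived impact on referral decisions, bidirectional communication".

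Study Design places the surveys inside the qualitative component, so the same rule governs the provider satisfaction and usability survey, a secondary outcome in Table 2.

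**The concern.** The eligibility rule is written from the sender's side of a two-sided system. Several groups the protocol intends to hear from do not send referrals in the ordinary course of their work, so the rule and the sampling plan cannot both be followed.

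The receiving side matters here. Under Outcomes, the receiving specialist decides whether a referral was unnecessary, and response time ends at specialist acknowledgment. Unanswered requests and acceptance or decline are also receiving-side behaviour. The convergent design is meant to set qualitative findings beside these results, yet the staff who generate them would mostly not be eligible to explain them.

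The rule also selects on adoption. Anyone trained on the app who never sent a referral is excluded by definition, although barriers to adoption are a stated topic. The protocol itself lists differences in digital literacy and connectivity as limitations, and staff stopped by those problems are the ones left out.

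**Working it through.** No formula applies and the protocol gives no figure to reproduce. The check sets the rule against the protocol's own account of who does what.

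**Who makes referrals.** Table 1 (Intervention) gives the user group of the electronic referral form as "Referring physicians, nurses, and medical officers". The user group for automated notifications is "Receiving specialists and bed managers". Figure 1 has the on-duty emergency physician at the tertiary hospital reviewing the request and accepting, discussing or rejecting it. Participants and Recruitment describes "bed managers, and administrative personnel who have access to referral dashboards to monitor and coordinate".

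**Applying the rule to each group.**

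| Group | Role in the protocol | Wanted in the sample? | Eligible under the stated rule? |
|---|---|---|---|
| Referring physicians, medical officers, nurses | Complete the referral form | Yes (participant list; physician and nurse strata) | Yes, after one referral |
| Receiving specialists at the tertiary hospitals | Get notifications, respond, advise | Yes (consultants in participant list; tertiary stratum) | Only if they have also sent a referral |
| Bed managers | Get notifications | Yes (participant list) | No, by role |
| Administrators | Track referrals, watch dashboards | Yes (participant list and a named stratum) | No, by role |
| Trained staff who never referred | None recorded | Not named, but relevant to barriers to adoption | No, by definition |

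**Number of places.** The plan anticipates 20 to 30 interviews and between 4 × 6 = 24 and 6 × 8 = 48 focus group participants. These totals do not depend on the rule. What the rule changes is who may fill them.

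**Does another section widen the rule?** No. Nothing elsewhere in the article admits providers who receive, coordinate or never use the platform. The wording says eligible *if*, not *only if*, but as the sole provider criterion besides consent it operates as a requirement.

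**Reach.** Because the surveys sit in the qualitative component, the rule also decides who contributes to the satisfaction and usability means and SDs in Table 2. The quantitative census of referral records has its own criteria and is untouched.

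**The case against.** The case for leaving the text alone has several parts, and some of it stands.

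- **Tertiary clinicians are not barred outright.** Nothing says they cannot send a referral, and Figure 1 allows for onward referral after a rejection. A reader might infer that the tertiary stratum would be nearly empty. The document does not support that; it supports only that tertiary staff qualify through sending and not through their main role. Physicians, nurses and the primary and secondary levels are not blocked.
- **The topic domains are not left without anyone to speak to them.** Table 1 lists referring professionals as users of the two-way communication function, and a single referral is enough to qualify, so reluctant or lapsed users can describe barriers. What is lost is the receiving-side view and the view of people who never used the app: the domains become one-sided.
- **Restricting usability scores to users is defensible.** Someone who has never opened the platform cannot rate its usability. A reader might infer that acceptability is biased upwards by some stated amount. The article gives neither the share of non-users nor their scores, so no size can be given, and the direction is plausible and not shown. The same reasoning defends requiring some use before the survey planned within two weeks of deployment. It does not defend counting only the sending of a referral as use.
- **The participant list sets no quota.** It says the study will engage bed managers and consultants, while the strata are fixed only in the sampling section. This weakens the point for bed managers slightly, but administrators are a named stratum, so the contradiction remains.

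**Conclusion.** The point holds as a conflict within the current text. The eligibility rule, followed literally, leaves the administrator stratum unfillable, excludes bed managers, admits receiving specialists only when they happen also to have sent a referral, and limits the evidence on barriers to people who got past them at least once.

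This rests on two readings: that the single stated criterion acts as a requirement, and that Table 1 and Figure 1 describe the roles correctly. It is firmest for administrators and bed managers and weaker for receiving specialists.

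The consequence is confined to the qualitative strand and the provider survey outcome. Neither primary outcome nor its analysis changes, though the explanation of both would come mainly from the sending side. The effect on survey scores cannot be quantified from the document. The point should be corrected before recruitment, which had not begun when the article was submitted.

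**What to change.** Reword the provider criterion in Eligibility Criteria so that any provider, bed manager or administrator at a participating facility who holds a platform account or was trained on it is eligible, whether as sender, receiver or dashboard user. Then:

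- In Sample Size and Sampling, purposively include some low users or non-users in the interviews on barriers, within the anticipated 20 to 30.
- Keep platform usability scores to people who have used the platform in any role, so that non-users are not asked to rate what they have not seen.
- Report provider survey scores by role.

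The cost is small edits to the eligibility and sampling text and a reporting line for the survey outcome. Because recruitment runs to saturation, hearing from more groups may need a few more interviews than anticipated. Acceptability findings may also come out less favourable.

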### Sample Size and Sampling

The quantitative part will use a census-based cohort design: all the referral records created via the platform over the 6-month pilot will be considered. According to the administrative referral logs of LRH, KTH, and HMC, it is estimated that 5000 to 7000 emergency referrals will be made. As the sample size of a census-based implementation study cannot be calculated using formal power, the rationale behind the sample size is the expected volumes of institutional referrals. For the qualitative component, health care providers will be selected using stratified purposive sampling to ensure representation across facility levels (primary, secondary, and tertiary), clinical roles (physicians, nurses, and administrators), and geographic locations (urban and rural). Recruitment will continue until thematic saturation is reached, with an anticipated sample of 20 to 30 individual interviews and 4 to 6 focus group discussions involving 6 to 8 participants each. Patients and attendants will be recruited using convenience sampling at the time of referral completion.

### Outcomes

Primary outcomes are change in the proportion of unnecessary referrals (defined as referrals where the receiving specialist determines that the patient could have been managed at the referring facility without transfer) and change in referral initiation–to-response time. Secondary outcomes are change in bed use, number of unanswered referral requests, referral acceptance and decline rates, number of cases managed through remote advice without transfer, patient mortality among emergency referrals where feasible, referral-related costs where feasible, patient and health care professional satisfaction, and platform usability (Table 2).

**Table 2 table2:** Outcome definitions, data sources, and analysis plan.

Outcome	Definition	Data source	Analysis plan
Change in unnecessary referral rate	Referrals deemed manageable at the referring facility without transfer	Platform records+specialist response field	Chi-square test and multivariable logistic regression
Change in referral initiation–to-response time	Interval from referral submission to specialist acknowledgment (min)	Platform time stamps	2-tailed *t* test or Mann-Whitney *U* test and multivariable regression
Change in bed use	Proportion of beds occupied at the receiving facilities	Platform dashboard+hospital records	Descriptive statistics and pretest-posttest comparison
Unanswered referral requests	Referrals without documented specialist response	Platform records	Frequency and rate calculation
Proportion of referrals answered within the urgency window	Percentage of referrals receiving a specialist response within predefined urgency-specific response targets	Platform time stamps	Frequencies, percentages, and chi-square test comparison
Referral acceptance and decline rate	Proportion of referrals accepted vs declined by the receiving facility	Platform records	Frequencies and chi-square test
Cases managed through remote advice	Referrals resolved via bidirectional specialist advice without transfer	Platform communication logs	Frequency and descriptive subgroup analysis
Patient satisfaction	Patient and attendant survey domain score	Structured survey (Multimedia Appendix 1)	Means and SDs and Likert distribution
Health care professional satisfaction and usability	Health care professional survey domain score	Structured survey (Multimedia Appendix 1)	Means and SDs and thematic integration

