### Study Setting

The research will be carried out at various levels of the Pakistani public health care system in KP. Primary care is provided by tehsil (subdistrict-level) hospitals and basic health units, secondary care is provided by district headquarters hospitals, and tertiary care is provided by Medical Teaching Institutions (MTIs). The 3 large tertiary care MTIs involved in this study are LRH, KTH, and HMC, all in the provincial capital, Peshawar.

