### Data Collection

Quantitative data will be collected automatically by the digital platform, recording referral time stamps, referral reason, urgency category, facility identifiers, bed availability status, and referral outcome. Preimplementation historical data will be extracted from paper registers at participating institutions. Health care professional surveys will be administered at 2 time points: within 2 weeks of deployment and at the end of the 6-month period. Patient surveys will be administered at the point of referral completion. Semistructured interviews will be conducted at midimplementation and at end of study. Focus group discussions will be held at approximately 3 months after deployment. Data quality will be checked through double-entry verification of a random 10% sample and monthly data monitoring committee reviews.

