### Data Analysis

Quantitative analysis will use SPSS (version 28; IBM Corp). Descriptive statistics, normality testing, pretest-posttest paired comparisons (2-tailed t test or Wilcoxon signed-rank test), chi-square or Fisher exact tests, and multivariable logistic regression will be conducted. A *P* value of less than .05 will be the significance threshold. Missing data will be handled using complete-case analysis (<10% missing) or multiple imputation (>10% missing). Historical referral data from participating institutions covering the 6 months immediately preceding platform deployment (December 2025-May 2026) will serve as the preimplementation comparison period.

Qualitative analysis will follow the six-step reflexive thematic analysis framework by Braun and Clarke [15]: (1) familiarization with the data, (2) generation of initial codes, (3) search for themes, (4) review of themes, (5) definition and naming of themes, and (6) production of the report. Interviews and focus group discussions will be audio recorded and transcribed verbatim prior to analysis. Two researchers will independently code the transcripts; coding disagreements will be resolved through discussion and consensus. Reflexive memos and an audit trail will be maintained throughout the analytical process. Recruitment will continue until thematic saturation is achieved.

Quantitative and qualitative datasets will first be analyzed independently, and results will subsequently be merged during the interpretation phase using a convergent mixed methods approach. Joint display matrices will be used to facilitate integration. Merged findings will be examined for convergence, complementarity, and divergence between the quantitative and qualitative strands.

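### The chi-square test named for the unnecessary-referral primary outcome treats clustered referrals as independent, so its P value is too small if facility effects or facility mix shift between periods

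*Protocol article*

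**What the plan says.** The Outcomes section defines an unnecessary referral by a clinician's decision: "referrals where the receiving specialist determines that the patient could have been managed at the referring facility without transfer". Table 2 assigns to this outcome "Chi-square test and multivariable logistic regression". The Data Analysis section repeats the methods for the study as a whole ("chi-square or Fisher exact tests, and multivariable logistic regression will be conducted") and sets the threshold: "A *P* value of less than .05 will be the significance threshold". It also lists paired pre-post comparisons, but Table 2 does not assign one to this outcome.

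The unit counted is the referral record. For the pilot, "it is estimated that 5000 to 7000 emergency referrals will be made". These come from primary and secondary facilities, whose number is not given ("Primary care is provided by tehsil (subdistrict-level) hospitals and basic health units, secondary care is provided by district headquarters hospitals"), and on the receiving side "The 3 large tertiary care MTIs involved in this study are LRH, KTH, and HMC".

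The comparator is the paper-register data for December 2025 to May 2026. The pilot starts in June 2026. The Results overview and Table 3 describe entry by tier: primary and secondary facilities first, the tertiary hospitals from July. The platform will be "recording referral time stamps, referral reason, urgency category, facility identifiers, bed availability status, and referral outcome", so a facility identifier exists for the pilot data.

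The article nowhere mentions a random effect, generalized estimating equations, cluster-robust standard errors or a facility-level analysis. The limitations do not mention clustering.

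**The concern.** Referrals from one facility share its staffing, equipment and case mix. Referrals judged by one specialist share that specialist's threshold. Outcomes within these groups are therefore likely to be correlated, and a facility's underlying rate can move between one half-year and the next for reasons unrelated to the platform. The chi-square test attributes all variation to independent records and makes no allowance for such movement.

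At stake is a primary result. With thousands of records the chi-square standard error is small, so a modest shift in a few busy facilities, or in which facilities contribute records, could cross the .05 threshold and be read as a platform effect. The article says the findings may be used to justify wider implementation.

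**Working it through.** The article gives no power calculation, baseline rate, ICC or design effect, so there is no figure of its own to reproduce. The figure of 5,000-7,000 is a volume forecast.

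**Inputs from the article:** two-period comparison; significance threshold .05 (taken as two-sided for the chi-square test); N = 5,000-7,000 referrals in the pilot; 3 receiving hospitals.

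**Assumptions:** pre-period N equal to the pilot N; K = 20-60 referring facilities of equal size, the same ones in both periods; ICC 0.01-0.05; cluster autocorrelation (CAC, the correlation of a facility's effect between periods) 0.8, then varied.

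**Formula.** Let m = N/K be referrals per facility per period. A facility effect that is constant over time cancels in the pre-post difference; the part that changes does not. The true variance of the difference, relative to what the chi-square test assumes, is

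DEFF = (1 − ICC) + m × ICC × (1 − CAC)

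and the true type I error of the nominal 5% test is

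2 × [1 − Φ(1.96/√DEFF)].

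**Ends of the assumed range at CAC 0.8**
- Low: N = 5,000, K = 60, m = 83.3, ICC 0.01. DEFF = 0.99 + 83.3 × 0.01 × 0.2 = 1.16; type I error 6.8%.
- High: N = 7,000, K = 20, m = 350, ICC 0.05. DEFF = 0.95 + 350 × 0.05 × 0.2 = 4.45; type I error 35%.

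**Sensitivity to the CAC, same two scenarios**

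| CAC | Low: DEFF, type I error | High: DEFF, type I error |
|---|---|---|
| 1.0 | 0.99, 4.9% | 0.95, 4.4% |
| 0.95 | 1.03, 5.4% | 1.83, 15% |
| 0.8 | 1.16, 6.8% | 4.45, 35% |
| 0.5 | 1.41, 9.8% | 9.70, 53% |

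**Check by simulation.** The chi-square test was simulated under no platform effect (5,000 records per period, assumed rate 0.40, 4,000 runs per scenario). With 30 facilities and CAC 0.8 it rejected in 9.1% of runs at ICC 0.01 and 22.9% at ICC 0.05; the formula gives 8.8% and 22.6%. With 100 facilities it rejected in 6.5% and 10.1%. With CAC 1 and an identical facility mix, rejection stayed at 4%-5%.

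**Facility mix.** Stable facility effects do not protect the test if the mix changes. With CAC 1 but facility shares drawn separately for each period (coefficient of variation 0.5), 30 facilities gave 10%-25% and 100 facilities gave 6%-12% over the same ICC range.

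**The case against.** Four points can be made for the plan.

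1. *The regression may be clustered.* The article says only that a multivariable logistic regression will be run. A reader might infer that it is an ordinary one and that the facility identifiers will go unused. The text supports neither: covariates and variance method are unspecified, and an analysis plan not shown could supply a facility term. This stands, and the type I errors above apply only to an analysis without one. It does not rescue the chi-square test, which the article itself names for a primary outcome and which a clustered regression elsewhere would not repair.

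2. *Paired comparisons are planned.* Different episodes are referred before and after, so the natural unit for pairing would be the facility. But the article does not say so, and Table 2 does not use pairing for this outcome. The unit of analysis is left unclear.

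3. *The size rests on assumptions.* This stands. The number of facilities, ICC, CAC and pre-period count are not in the article. At the mild end the error is close to 5%, and with full stability there is no inflation. One therefore cannot say that drift will often be declared a platform effect.

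4. *It is a census.* Full enumeration does not make records independent, and the plan still tests at .05.

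A stronger reading takes the 3 receiving hospitals as the clusters. At ICC 0.01 and CAC 0.8 the formula gives DEFF 4.32 (m = 1,667) to 5.66 (m = 2,333), a type I error of 35%-41%. This should not be counted as inflation that a better model would remove: hospital-by-period drift cannot be estimated reliably from 3 hospitals. Nor can a specialist-level figure be given. The article states neither how many specialists will judge referrals nor that a specialist identifier is recorded.

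**Conclusion.** The concern holds for the chi-square test on the unnecessary-referral outcome. This is a method the article fixes, not a detail it leaves open. The direction is clear: P values are too small if facility effects or facility mix shift between periods. Phasing by tier and the change of calendar half-year make some shift likely.

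The size is uncertain. The range of about 7%-35% holds only for 20-60 equal-sized referring facilities, ICC 0.01-0.05, CAC 0.8 and 5,000-7,000 referrals in each period. It falls to about 5% with stable effects and mix, and rises as the CAC falls. The unpaired response-time test in Table 2 (t or Mann-Whitney) makes the same independence assumption; no figure was computed for it.

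**What to change.** Before data collection starts, amend Table 2 and the Data Analysis section as follows.

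- Make the primary analysis of unnecessary referrals a mixed-effects logistic model with period and receiving hospital (3 levels) as fixed effects, and referring facility and facility-by-period as random effects, with small-sample degrees of freedom. A facility random intercept alone is not enough, because it ignores change between periods. A paired facility-level pre-post analysis is an acceptable alternative.
- Use the same clustering structure for response time.
- Keep the chi-square test as descriptive only.
- Report the period effect separately for each of the 3 hospitals. State as a limitation that hospital-by-period and specialist-level drift cannot be reliably modelled with 3 hospitals; the hospital fixed effect does not absorb it.
- Confirm that the referring-facility identifier is also extracted from the paper registers. The article lists it only for platform data, and the model needs it in both periods.

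The cost is analysis wording plus that check on register extraction. The downside is wider confidence intervals.

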### Platform Development and Validation

The KP MTI Referral Application was developed through a user-centered design approach informed by continuous stakeholder engagement and iterative refinement. Structured requirement-gathering sessions were conducted with neurosurgeons, emergency physicians, medical officers, nurses, bed managers, hospital administrators, and IT personnel from participating institutions to ensure alignment with existing referral workflows and operational requirements.

A beta version of the platform was deployed in a controlled testing environment at LRH. Beta testing involved volunteer health care providers, including physicians and bed managers, who participated in simulated trauma referral scenarios. Testing evaluated successful referral submission, transmission of clinical information and images, notification delivery, specialist response receipt, referral tracking functionality, and overall usability. End-to-end workflow testing confirmed that referrals could be submitted successfully, notifications were delivered appropriately, specialist responses were received and tracked, and referral progress could be monitored in real time.

Feedback obtained during beta testing informed iterative platform refinements. Major modifications included simplification of the referral form interface, optimization of image-sharing workflows, and enhancement of the notification system through automated reminder alerts repeated every 10 minutes until a specialist response was documented. Validation testing was subsequently conducted against predefined functional and clinical requirements before pilot deployment. Formal training materials and implementation support resources were also developed for frontline users prior to rollout.

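### The response-time primary has no value for unanswered referrals, and the plan's only applicable rules would drop them or impute a reply that never came; the comparison is biased when the unanswered share differs between periods

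*Protocol article*

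**What the plan says.** Under Outcomes, Table 2 of the protocol article gives the response-time primary as "Interval from referral submission to specialist acknowledgment (min"), with platform time stamps as its data source. Its analysis is "2-tailed *t* test or Mann-Whitney *U* test and multivariable regression".

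The same table has a separate secondary row for "Referrals without documented specialist response", summarised by frequency and rate only. Another row gives the "Percentage of referrals receiving a specialist response within predefined urgency-specific response targets", compared by chi-square test.

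Two general rules could touch a referral with no interval. Eligibility Criteria: "Records will be omitted when they are not complete, marked as duplicates, or created in the process of system testing". Data Analysis: "Missing data will be handled using complete-case analysis (<10% missing) or multiple imputation (>10% missing"). Neither mentions unanswered referrals, and the article names no censoring, worst-rank or composite rule.

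Platform Development and Validation describes "automated reminder alerts repeated every 10 minutes until a specialist response was documented". Data Collection says that the historical comparator comes from paper registers.

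**The concern.** An unanswered referral is not a referral whose response time was lost. It is the worst result the outcome can take, or a time known only to exceed the period of observation. A t test or a regression on minutes cannot hold it. A Mann-Whitney test can, but only if someone assigns it a rank, and the article assigns none.

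That leaves the two general rules. If the record counts as incomplete it is omitted. If the interval counts as missing, the referral is deleted when less than 10% is missing and receives an imputed reply time when more than 10% is. Either way the primary comparison describes answered referrals, or treats all referrals as if answered.

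This matters because being answered happens after the intervention and is something the intervention targets. If reminders turn silence into late replies, those replies enter only the post-deployment sample and make the platform look slower. If slow requests drop out unanswered, the period that loses them looks faster. Both distort a primary outcome.

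**Working it through.** **Inputs.** The documents supply the outcome definition, the tests, the threshold ("A *P* value of less than .05 will be the significance threshold") and an expected 5000 to 7000 referrals in the pilot. They give no unanswered share, response-time distribution or effect size, so there is no plan figure to reproduce and everything below is assumed: equal volume n in both periods; prompt replies lognormal, median 60 min, log-SD 1, the same in both periods; unanswered share u0 before and u1 after; the difference r = u0 − u1 consists of rescued referrals that now get a reply.

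**Formulas.** Let q be the chance that a rescued reply is slower than a prompt one. The Mann-Whitney effect is P(post slower than pre), with ties counted half; 0.5 means no difference and above 0.5 means the platform looks slower.

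- Answered referrals only: A = 0.5 + r(q − 0.5)/(1 − u1).
- All referrals, unanswered ranked longest: B = 0.5 − r[(1 − u0)(1 − q) + u0/2].
- For lognormal times, q = Φ(ln(late median/60)/√(1 + s²)), where s is the log-SD of late replies.
- z = (A or B − 0.5)/√((m + k + 1)/(12mk)), where m and k are the numbers analysed in each period (tie correction ignored).

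B is below 0.5 whenever anyone is rescued. A is above 0.5 whenever rescued replies tend to be slower than prompt ones. So late rescues always push the two analyses in opposite directions; the shares and speeds decide only whether each reaches significance.

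**Results.**

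1. *Equal shares (15% and 15%), same distribution.* r = 0, so A = B = 0.5. No bias.
2. *20% to 5%, rescued replies at ordinary speed (q = 0.5), n = 6000.* A = 0.5. B = 0.5 − 0.15(0.80 × 0.5 + 0.10) = 0.425, z = −14.2. The answered-only test misses a clear benefit.
3. *9% to 2%, late median 240 min, s = 0.5, n = 5000.* q = Φ(1.386/1.118) = 0.8925. A = 0.5 + 0.07 × 0.3925/0.98 = 0.528, z = 4.7. B = 0.5 − 0.07(0.91 × 0.1075 + 0.045) = 0.490, z = −1.7, P about .08. The answered-only test shows a spurious worsening; the all-referral test shows no significant benefit. At n = 7000 B is the same and P is close to .05.
4. *15% to 2%, same late replies, n = 5000.* A = 0.5 + 0.13 × 0.3925/0.98 = 0.552, z = 8.6. B = 0.5 − 0.13(0.85 × 0.1075 + 0.075) = 0.478, z = −3.7. Significant in opposite directions.
5. *20% to 5%, late median 240 min, s = 0.7, n = 6000.* q = Φ(1.386/1.221) = 0.872. A = 0.5 + 0.15 × 0.372/0.95 = 0.559, z = 10.4. B = 0.5 − 0.15(0.80 × 0.128 + 0.10) = 0.470, z = −5.8. A significant reversal.

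**Scenario 5 in minutes.** By simulation, the answered-only median rises from about 60 to 74 min and the mean from about 99 to 132 min, although no referral is answered later than before. Over all referrals, the share answered by 4 h rises from 0.80 × 0.917 = 73% to 73% + 0.15 × 0.5 = 81%, and by 8 h from 79% to 91%.

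**Opposite direction.** If the slowest 10% of replies simply became unanswered, the answered-only mean would fall from 99 to 67 min (98.9 × Φ(1.282 − 1)/0.9) with nobody answered sooner.

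Simulations of scenarios 1 and 3 to 5 agree with these formulas. The multiple-imputation branch was not simulated; the objection to it is that the value being imputed does not exist.

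**The case against.** **The article never says that no response is missing data.** This stands. It gives non-response its own outcome row, which could equally mean that it is an observed state. That the general rules would apply is an inference from the definition and from the absence of any other rule.

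**Scoring non-responders in a named test is a detail for an analysis plan.** This stands in part. Ranking them longest fits the Mann-Whitney option already listed. But the article also fixes a t test option, a regression on minutes, an exclusion of incomplete records and a missing-data rule, and none of these can carry an unanswered referral correctly.

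**The within-window percentage already covers it.** Read naturally, its denominator is all referrals and unanswered ones count as failures. It would partly expose a misleading primary result, but it is secondary and does not repair the primary test.

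**The magnitude depends on chosen inputs.** This stands. A median of 240 min for rescued replies means 240/10 = 24 reminders for the typical case, which is slow. The case in which slow requests are lost has no evident mechanism on a platform that keeps reminding.

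**The baseline may not support any version of this comparison.** This stands as a limit on the remedy. The only listed source is platform time stamps, the comparator is paper registers, and Strengths and Limitations concedes that these may be incomplete.

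A reader might infer that the plan deliberately restricts the primary to answered referrals, or that its result will be reversed. The documents support neither: the restriction follows from rules that do not name unanswered referrals, and a significant reversal needs particular shares and late replies that the documents do not give.

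**Conclusion.** The defect holds. A primary outcome is defined on an interval that exists only after acknowledgment, and the stated rules that could reach an unanswered referral would either remove it or invent its reply. The comparison is therefore biased whenever the unanswered share differs between periods, a difference that the reminder feature is designed to produce.

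The size is unknown. Under assumed inputs it runs from none, through a missed benefit and a spurious worsening, to a significant reversal. At the expected 5000 to 7000 records, even a modest artefact such as 0.528 against 0.5 would be reported as highly significant. The conclusion that the handling must be fixed does not depend on which scenario is true; any claim about direction or size does.

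**What to change.** Define the response-time primary on all submitted referrals, followed to one fixed horizon that is the same in both periods. Then do one of the following:

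- keep the planned Mann-Whitney test and rank referrals unanswered at the horizon longest; or
- censor them at the horizon and report Kaplan-Meier curves or the restricted mean time to response, with a time-to-event model for the adjusted analysis.

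State that the absence of a documented response is an outcome and is not subject to the incomplete-record exclusion or to the complete-case and imputation rule. State also that the denominator of the within-window percentage is all referrals.

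The cost is a change of analysis wording, best made before deployment in June 2026, and a reported time that may look less favourable than one among answered referrals. In the pre-deployment period the fix works only as far as the paper registers record request times and non-replies. The article should say what the registers hold and state that limit.
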